#### Measurement and valuation of resource use (within-trial analysis)

Five main areas of resource use will be included in the within-trial analyses (table 1): delivery of the implementation strategy by the research team, delivery of the intervention by the health professionals, patient healthcare utilisation, use of aged care services and use of disability services. The costs of implementation and intervention delivery will be collected using trial logs, informed by the Costing implementation strategies (Cost-IS) instrument.^18^ Data to be collected on healthcare utilisation will include ambulance, hospital and community-based health service use, as well as use of medications using data linkage through the Centre for Health Record Linkage and Services Australia. Data related to the use of aged care and disability services will be collected using data linkage through Aged Care and the National Disability Insurance Scheme (NDIS). Costs will be valued using relevant state and national data.

**Table 1 T1:** Measurement and valuation of resource utilisation

Resource items	Source of utilisation estimates	Unit of measurement	Valuation (source of unit cost)
Healthcare utilisation			
Ambulance use	Data linkage (through CHeReL)	Number of calls, cost/use	NSW ambulance fees and charges
Emergency department presentation	Data linkage (through CHeReL)	Number of emergency department presentations, (NWAU)/presentation	Urgency-related group classification system
Non-admitted patient activity	Data linkage (through CHeReL)	Number of episodes of care, NWAU/episode	Tier 2 non-admitted classification
Hospital admission	Data linkage (through CHeReL)	Number and length of admission, NWAU/admission	Australia refined diagnosis-related groups
Medicare Benefits Schedule use	Data linkage (through Services Australia)	Occasions of use, duration/occasion of use, cost/occasion of use	Medicare Benefits Schedule
Pharmaceutical Benefits Scheme use	Data linkage (through Services Australia)	Number of items, cost/item	Pharmaceutical Benefits Scheme
NDIS service use	Data linkage (through NDIS)	Occasions of use, duration/occasion of use, cost/occasion of use	NDIS pricing arrangements and price limits
Aged care service use	Data linkage (through AIHW)	Occasions of use, duration/occasion of use, cost/occasion of use	Aged care subsidies and supplements
Implementation support costs			
Staff costs			
Research staff time to conduct service mapping, planning and delivering support to health service staff (clinical teams) and updating website resources.	Trial records	Number of hours, cost/hour	University of Sydney enterprise agreement
Experts/clinical mentor time in delivering training and workshops to clinical teams.	Trial records	Number of hours, cost/hour	University of Sydney enterprise agreement/ NSW health award for the relevant year
Health service staff time participating in the service mapping process, participating in support from research staff, training/workshop activities and accessing resource and training hub.	Trial records	Number of hours, cost/hour	NSW health award for the relevant year
Travel costs	Trial records	Distance travelled, cost/km	Cents per kilometre method as per the Australia Taxation Office
Material production costs (ie, printing)	Trial records	Number of pages, cost/page	Cost as per invoice
Equipment costs (eg, activity monitors)	Trial records	Number of items, cost per item	Cost as per invoice
Website maintenance costs	Trial records	Cost/month	Cost as per invoice
Intervention delivery costs			
Health service staff time to deliver physical activity promotion.	Self-report questionnaire	Number of hours, cost/hour	NSW health award for the relevant year
Research staff time to deliver the Physical Activity Linkage Programme.	Trial records	Number of hours, cost/hour	University of Sydney enterprise agreement

AIHW, Australian Institute of Health and Welfare; CHeReL, Centre for Health Record Linkage; NDIS, National Disability Insurance Scheme; NSW, New South Wales; NWAU, National Weighted Activity Unit.

#### Analysis and sensitivity analysis (within-trial analysis)

Data analysis will be conducted using Stata V.16 (Stata Corp, College Station, Texas). The within-trial cost-effectiveness and cost-utility analyses will include total costs and effects over the 6-month trial follow-up period.

Incremental cost-effectiveness ratios (ICERs) will be calculated to determine the additional costs required to achieve the additional health outcomes associated with the implementation strategy. This will be measured in terms of gains in patient PA participation and health professional PA promotion (cost-effectiveness analysis) and QALYs (cost-utility analysis). The following formula will be used to calculate the ICER:

$$ICER=\frac{Implementation\;support\;costs\;-Usual\;care\;cost\;costs}{Implementation\;support\;effects-Usual\;care\;effects}$$

Clustering will be considered to take into account similarity within and difference between clusters when calculating the incremental costs and health outcomes.^19^ To examine uncertainty around the ICERs for PA participation, QALYs and PA promotion, bootstrapping with at least 1000 iterations will be used to estimate a distribution around costs and health outcomes, with results to be plotted on a cost-effectiveness plane. Bootstrapping will also be used to estimate 95% CIs around the ICERs. A cost-effectiveness acceptability curve will be generated to explore the probability of the intervention being cost-effective at different willingness-to-pay thresholds. To assess the robustness of results, one-way and multiway sensitivity analyses will be undertaken to see how study results change when using different assumptions and parameters (eg, under-reporting or over-reporting of self-reported PA, unit prices used for valuing resource use, methods for handling missing data).^20 21^ Cost and effectiveness outcomes will be presented as outlined in table 2.

**Table 2 T2:** Cost and effectiveness outcomes and ICERs in base case, sensitivity and subgroup analysis

	Intervention	Usual care	Mean difference (bootstrapped 95% CI)
Base case analysis			
Total cost per participant ($A) (mean, SD)			
Total QALYs (mean, SD)			
ICER for QALYs			
Proportion of participants meeting MVPA guidelines (n, %)			
ICER for MVPA			
Scenario analysis—no extra staff cost			
Total cost per participant ($A)			
Total QALYs (mean, SD)			
ICER for QALYs			
Proportion of participants meeting MVPA guidelines (n, %)			
ICER for MVPA			
Sensitivity analysis			
Total cost per participant ($A) (mean, SD)			
Total QALYs (mean, SD)			
ICER for QALYs			
Proportion of participants meeting MVPA guidelines (n, %)			
ICER for MVPA			
Subgroup analysis			
Total cost per participant ($A) (mean, SD)			
Total QALYs (mean, SD)			
ICER for QALYs			
Proportion of participants meeting MVPA guidelines (n, %)			
ICER for MVPA			

* Intervention includes the delivery of the implementation strategy by the research team to clinical teams and the delivery of physical activity promotion by the clinical staff to their patients.

ICER, incremental cost-effectiveness ratio; MVPA, moderate-to-vigorous physical activity; QALY, quality-adjusted life year.

The base case analysis will include the costs associated with health professional time spent receiving implementation support and delivering PA promotion to account for opportunity cost. However, health professionals will be receiving implementation support during their usual working hours and delivering PA promotion as part of their routine practice. As such, a scenario analysis will be conducted where health professional time will be excluded from the total costs used to calculate the ICERs. While this approach does not account for opportunity cost, consultation with health managers indicates that such an analysis would be useful to inform the implementation of this programme.

Scenario analyses will be conducted to determine the effect of adopting different perspectives on cost-effectiveness and cost-utility. The perspectives of state and federal government funders will be considered. Exploratory subgroup analysis will be conducted in line with the analyses planned for the effectiveness outcomes (ie, subgroup analysis for paediatric participants aged 5–17 years to investigate the effect of PA promotion on PA among children and young people)^8^ and will also include cost-effectiveness and cost-utility according to socioeconomic status (as indicated by participant postcode). Subgroup analysis will be conducted for participants according to the Index of Relative Socioeconomic Disadvantage. A cut-off point of quintile two or lower will be used to represent areas with lowest Socio-Economic Indexes for Areas scores.^22^

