**Methods and analysis:**

We will conduct a cost-effectiveness and cost-utility analysis from the perspective of the healthcare, aged care and disability funder. The time horizon will be 6 months for the within-trial analysis and 2 years for the modelled analysis. Data on intervention costs will be collected using trial records. Data on healthcare utilisation will be collected using data linkage. Incremental cost-effectiveness ratios (ICERs) will be reported for physical activity and quality-adjusted life years outcomes. Bootstrapping will be used to explore uncertainty around the ICERs and estimate 95% CIs. Results will be presented on a cost-effectiveness plane. The probability that the intervention would be cost-effective at varying willingness-to-pay thresholds will be presented using a cost-effectiveness acceptability curve.

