### *PROMOTE-PA *trial

#### Study population

Patient participants will be 720 individuals aged 5 years and above living in the community who are receiving outpatient care from health professionals (n=30 clusters) at one of the multiple participating local health districts, a specialty children’s health network or a private clinic in New South Wales, Australia.

Study recruitment commenced in February 2024 and is expected to finish by December 2025. Participant follow-up is expected to be completed in December 2026.

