### Within-trial analysis

The time horizon for the within-trial analysis is 6 months, representing the length of follow-up for patient participants in the trial. Costs and health outcomes will not be discounted as the time horizon is less than 12 months. The analysis will follow an intention-to-treat approach.

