#### Measurement and valuation of health outcomes (within-trial analysis)

Intervention (patient-level) and implementation (health professional-level) outcomes will be used in this economic evaluation. The patient-level outcomes used will be the self-reported time spent in moderate-to-vigorous PA (MVPA) over the past week (reported in hours/week using a modified version of the PA vital sign)^13^ and QALYs (derived from the EuroQol 5-dimensions 5 level-version (EQ-5D-5L) or EuroQol 5-dimensions youth version (EQ-5D-Y)).^14 15^

The effectiveness outcome measure for the within-trial cost-effectiveness analysis will be the difference in proportion of participants achieving 150 min of MVPA per week in the intervention group, compared with the control group at 6 months.

The effectiveness outcome measure for the within-trial cost-utility analysis will be QALYs gained in the intervention group, compared with the control group over 6 months. Utility-based quality of life will be measured using the EQ-5D-5L^15^ in adults and the EQ-5D-Y^14^ in children and adolescents (aged 5–17 years). The EQ-5D-5L measure includes five dimensions: mobility, self-care, usual activities, pain/discomfort and anxiety/depression. Each item is rated on a five-level scale, ranging from no problems to extreme problems within each dimension. Australian scoring algorithms will be used to calculate a health utility score based on the EQ-5D-5L.^16^ The EQ-5D-Y includes the same five dimensions, reworded for relevance to children, but is instead scored on a 3-level scale. As an Australian scoring algorithm for the EQ-5D-Y has not yet been published, a valuation from a country with a similar population will be used (ie, the Netherlands).^17^ The health utility scores fall on a scale of 0.0 (dead) to 1.0 (perfect health). In the instance that a participant passes away during the trial, they will be assigned a health utility score of 0 from that point forth. Health utility scores at baseline and 3-month and 6-month follow-ups will be used to calculate QALYs using the following formula:

QALYs=healthutilityscore×timespentinhealthstate

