#### Analysis and sensitivity analysis (modelled analysis)

The modelled analysis results will be presented as incremental cost per QALY gained. Subgroup analysis will be conducted as per the effectiveness outcomes. Sensitivity analysis will be conducted to determine the robustness of the model. Monte Carlo simulation and probabilistic sensitivity analyses will be used to estimate a distribution around costs and health outcomes, with results to be plotted on a cost-effectiveness plane. The Monte Carlo simulation will also be used to estimate 95% CIs around the ICERs. A cost-effectiveness acceptability curve will be generated to explore the probability of the intervention being cost-effective at different willingness-to-pay thresholds.

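### 95% CIs around the ICERs are promised without condition; if the replicates straddle zero effect, the interval mixes dominant with dominated results and cannot be read as value for money

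*Protocol article*

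**What the plan says.** The section on within-trial analysis and sensitivity analysis defines the ICER as the cost difference divided by the effect difference. It then says: "To examine uncertainty around the ICERs for PA participation, QALYs and PA promotion, bootstrapping with at least 1000 iterations will be used", with the results shown on a cost-effectiveness plane. It adds: "Bootstrapping will also be used to estimate 95% CIs around the ICERs". An acceptability curve follows. The abstract repeats the commitment: "Bootstrapping will be used to explore uncertainty around the ICERs and estimate 95% CIs". For the 2-year model the wording is: "The Monte Carlo simulation will also be used to estimate 95% CIs around the ICERs".

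Table 2 has one interval column, whose heading begins "Mean difference (bootstrapped 95% CI". It spans the ICER rows as well as the rows for cost, QALYs and the proportion meeting the activity guideline, in the base-case, scenario, sensitivity and subgroup blocks.

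The article gives no rule for replicates with a zero or negative effect difference and mentions no net-benefit interval. The Economic evaluation overview says that an analysis plan for both analyses will be signed before data analysis begins.

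**The concern.** A confidence interval is useful when moving along it means moving from worse to better. The ICER has that property only while the effect difference keeps one sign. Across zero effect the ratio jumps from one infinity to the other. Beyond it, a negative ratio may mean cheaper and better (dominant) or dearer and worse (dominated). A positive ratio may mean paying for a gain (north-east quadrant) or saving at the price of a loss (south-west), and the decision rule reverses between those two.

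The setting makes a small denominator plausible. The plan states: "The time horizon for the within-trial analysis is 6 months, representing the length of follow-up for patient participants in the trial". A short horizon limits the QALYs that any utility gain can produce. The paediatric and low-socioeconomic subgroups will have larger standard errors than the whole trial. The activity and promotion ICERs are exposed in the same way if those differences are small.

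At stake is a printed interval that funders could take as a range of value for money when it is not one.

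**Working it through.** **What the article supplies.** It gives 720 patients, 30 clusters, a 6-month horizon, and utilities at baseline, 3 and 6 months. It gives no expected QALY difference, SD, intracluster correlation (ICC), cost SD, willingness-to-pay threshold or ICER interval, so there is no figure to reproduce. What follows tests the property of the interval under stated assumptions.

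**Step 1, algebra.** Dominated: 300 / (-0.01) = -30,000. Dominant: (-300) / 0.01 = -30,000. The number is the same and the conclusions are opposite.

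**Step 2, size of a 6-month QALY difference.** Assume equal baselines, a utility gain d present at 3 and 6 months, and area under the curve. The gain is 0.25 × d/2 + 0.25 × d = 0.375d. Hence d = 0.02 gives 0.0075 QALY and d = 0.05 gives 0.019. A difference of 0.03 QALY needs d = 0.03/0.375 = 0.08.

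**Step 3, one illustration (assumed).** The cost difference is A$300 (SE 250) and the QALY difference 0.010 (SE 0.008), independent and normal.
- P(QALY difference < 0) = Φ(-0.010/0.008) = Φ(-1.25) = 10.6%.
- P(cost difference < 0) = Φ(-300/250) = Φ(-1.2) = 11.5%.
- Dominated: 0.106 × 0.885 = 9.3%. Dominant: 0.894 × 0.115 = 10.3%. South-west: 0.106 × 0.115 = 1.2%.
- The 2.5th and 97.5th percentiles of the ratio, by numerical integration of P(C/E ≤ r), are about -A$262,000 and +A$332,000 per QALY.
- Incremental net monetary benefit at an assumed A$50,000 per QALY: 50,000 × 0.010 - 300 = A$200; SE = √[(50,000 × 0.008)² + 250²] = √222,500 = 472; 95% CI 200 ± 1.96 × 472 = -A$725 to A$1,125.

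**Step 4, varying the effect.** Assume 360 per arm, 24 per cluster (720/30), QALY SD 0.10, cost SD A$3,000, ICC 0.01 and cost difference A$300. The design effect is 1 + 23 × 0.01 = 1.23. The SE is SD × √(2/360 × 1.23), which is 0.0083 QALY and A$248. Percentiles are obtained as in Step 3; simulation with 200,000 draws agrees within about 4%.

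| QALY difference | Effect < 0 | Dominated | Dominant | Percentile interval of the ratio (A$/QALY) | Net benefit 95% CI at A$50,000 |
|---|---|---|---|---|---|
| 0 | 50% | 44% | 6% | -631,000 to 631,000 | -1,245 to 645 |
| 0.005 | 27% | 24% | 8% | -509,000 to 541,000 | -995 to 895 |
| 0.01 | 11% | 10% | 10% | -269,000 to 334,000 | -745 to 1,145 |
| 0.02 | 0.8% | 0.7% | 11% | -12,900 to 81,200 | -245 to 1,645 |
| 0.03 | 0.01% | 0.01% | 11% | -6,600 to 34,800 | 255 to 2,145 |

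In the last two rows practically every negative ratio means dominance, so the interval can be read.

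**Step 5, range over the assumptions.** With QALY SD 0.05 to 0.10 and ICC 0.01 to 0.05, P(effect < 0) is 11-32% at 0.005 QALY, 1-18% at 0.01 and about 0-3% at 0.02.

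**Step 6, subgroups.** If a subgroup held a quarter of the patients with the same design effect (assumed), the SE would double to 0.0165. At 0.01 QALY, P(effect < 0) = Φ(-0.01/0.0165) = 27%, against 11% in the whole trial.

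**The case against.** The strongest reply has four parts.

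*The article does not say how the limits are taken.* That is correct. Sorting ratios and taking percentiles is an inference, and an analysis plan commonly settles such detail. What stands against this is that the output itself is promised three times without condition, and any interval read from the ordered ratios has the problem. A plan that carries out this text as written inherits it.

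*The triggering condition is assumed.* This also stands. A reader might infer that the 6-month QALY difference will be near zero and the interval therefore meaningless. The documents give no effect or SD from which to show that, and at 0.02 to 0.03 QALY the interval is readable or nearly so. Nor does the 6-month argument carry over automatically to the 2-year model.

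*The valid displays are already planned.* This is true and important. The plane shows the quadrants. The acceptability curve is the probability that net benefit is positive at each threshold. Table 2 has separate intervals for cost and effect. A reader might infer that the economic analysis is invalid; these outputs show that it is not. They do not repair an ICER interval printed beside them.

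*The net-benefit interval may also cross zero.* It may, as in Step 3. But it is finite and ordered, and crossing zero has one meaning.

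Numerical coverage is not the complaint either: in simulation the percentile interval covered 96-98%. The fault is in its meaning.

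**Conclusion.** The point holds in a limited, conditional form. The article commits to ICER intervals whatever the sign of the effect difference, and such an interval does not describe value for money when a material share of replicates lies on each side of zero effect. For 6-month QALYs this is plausible: 1-32% of replicates would be on the wrong side for true differences of 0.005 to 0.01 QALY under the assumed SDs and ICCs. It is likelier in the smaller subgroups, and little or no problem from about 0.02 to 0.03 QALY upward.

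These figures rest on 1:1 allocation, normality, independent cost and effect differences, and assumed SDs, ICCs and threshold. Correlation would change the split between quadrants but not the share with negative effect. The consequence is confined to one reported quantity. It should be corrected before the analysis plan is signed, so that the presentation is not chosen after the replicates have been seen.

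**What to change.** Keep the plane, the acceptability curve and the separate CIs for cost and effect differences. Change the two statements on ICER intervals and the layout of Table 2 as follows.

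1. For the QALY analysis, add incremental net monetary benefit with a 95% CI at prespecified willingness-to-pay thresholds.
2. For every ICER (QALY, activity, promotion, subgroups and model), report a 95% CI only when the replicates lie almost entirely on the positive-effect side, for example at least 97.5%.
3. Otherwise, replace the interval in that Table 2 row with the share of replicates in each of the four quadrants.

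Because the rule is conditional, it can be applied to the 2-year model without assuming that its effect difference will be small. The 97.5% cut-off is a convention; another value would serve if fixed in advance.

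The cost is wording, table layout and slightly more reporting. No new data are needed. The downside is that some ICER rows will carry no interval.

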### Comparison of resource utilisation

The primary resource utilisation outcomes will be rates and cost of healthcare, aged care and disability service utilisation in both groups over 2 years. A breakdown of healthcare utilisation costs according to cost categories (emergency, admitted, non-admitted and ambulance data, Medicare Benefits Schedule/Pharmaceutical Benefits Scheme, NDIS and aged care services use) will also be reported.

Healthcare, residential aged care and disability resource utilisation and costs will be described using means, SD, medians and IQRs over the 2-year period. Rates of service use will be compared between groups using negative binomial regression.

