## Abstract

**Introduction:**

Physical activity has important benefits for the prevention and management of chronic diseases and healthy ageing. Health professionals have valuable opportunities to promote physical activity to a large group of people across the lifespan. Promotion of Physical Activity by Health Professionals is a hybrid type 1 effectiveness-implementation cluster randomised trial designed to evaluate the impact of physical activity promotion by health professionals (n=30 clusters) on physical activity participation in their patients (n=720). To inform the future implementation of this programme, we will be conducting a within-trial and modelled economic evaluation.

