### Economic evaluation overview

This economic evaluation will be conducted from the healthcare, aged care and disability care funders’ perspective. All costs will be valued in 2024 $A. Within-trial cost-effectiveness and cost-utility analysis will be conducted as part of the *PROMOTE-PA* study, to determine the incremental costs and incremental health outcomes of the implementation strategies for PA promotion compared with usual care. Data linkage will be used to determine and compare levels of healthcare utilisation among patients of health professionals receiving support for PA promotion compared with usual care over 2 years. Decision-analytical modelling will be used to determine the incremental costs and health outcomes with an extended time horizon of 2 years. The economic evaluation will be reported according to the Consolidated Health Economic Evaluation Reporting Standards.^12^ A statistical analysis plan for the within-trial and modelled analyses will be written and signed by the study authors prior to the commencement of data analysis.

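### The 2-year service-use comparison names negative binomial regression with no cluster adjustment stated, although 30 clusters are randomised

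*Protocol article*

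**What the plan says.** The article describes a cluster randomised trial with 30 clusters of health professionals and 720 patients. Under *Economic questions*, the level of healthcare utilisation over 2 years is one of the secondary questions.

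The section *Comparison of resource utilisation* defines the outcomes: "The primary resource utilisation outcomes will be rates and cost of healthcare, aged care and disability service utilisation in both groups over 2 years". Utilisation and costs are to be summarised descriptively. The one between-group method given is: "Rates of service use will be compared between groups using negative binomial regression".

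Clustering is mentioned once as an analysis matter, under *Analysis and sensitivity analysis (within-trial analysis)*: "Clustering will be considered to take into account similarity within and difference between clusters when calculating the incremental costs and health outcomes". The within-trial analysis has a 6-month horizon.

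On further specification, *Economic evaluation overview* says: "A statistical analysis plan for the within-trial and modelled analyses will be written and signed by the study authors". That section also introduces the linked 2-year utilisation comparison as a component of its own, but the sentence about the analysis plan does not name it.

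**The concern.** Patients of one clinical team are likely to resemble each other in service use. Teams come from several local health districts, a children's network and private clinics, and patients are aged 5 years and over. Negative binomial regression does not deal with this by itself. Its dispersion parameter absorbs extra variation between individual patients, not correlation among patients of the same team.

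The section on resource utilisation stands beside the within-trial and modelled sections, not inside either, so the clustering sentence does not carry over to it on its face. A reader who follows the text would fit a model to 720 patients as if they were independent. A difference in service use that only reflects differences between teams could then be reported as an effect of implementation support.

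**Working it through.** **Is there a figure to reproduce?** No. The article gives no ICC, event rate, dispersion, significance level or sample-size derivation for this comparison. Only the mean cluster size follows from the text; the ICC below is an assumption, shown over a range.

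**Inputs.** 720 patients and 30 clusters (article abstract and *Study population*), so the mean cluster size is m = 720/30 = 24. The nominal two-sided level is taken as 5%.

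**Formulas.**
- Design effect: DE = 1 + (m − 1) × ICC = 1 + 23 × ICC.
- Shortfall in the standard error if clusters are ignored: 1 − 1/√DE.
- True size of a nominal 5% test: 2 × (1 − Φ(1.96/√DE)).
- Effective sample size: 720/DE.

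Worked example at ICC 0.05: DE = 1 + 23 × 0.05 = 2.15; √2.15 = 1.466; shortfall 1 − 1/1.466 = 31.8%; 1.96/1.466 = 1.337, giving a size of 18.1%; effective sample 720/2.15 = 335.

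| Assumed ICC | DE | SE too small by | True size | Effective N |
|---|---|---|---|---|
| 0 | 1.00 | 0% | 5.0% | 720 |
| 0.01 | 1.23 | 9.8% | 7.7% | 585 |
| 0.02 | 1.46 | 17.2% | 10.5% | 493 |
| 0.05 | 2.15 | 31.8% | 18.1% | 335 |
| 0.10 | 3.30 | 45.0% | 28.1% | 218 |

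**Cross-check with the named model.** The design-effect formula is an approximation for counts, so ordinary negative binomial regression was also simulated. The settings were 15 against 15 clusters of 24, no true effect, an assumed mean of 2 events, dispersion 1.5, a normal team effect on the log scale, and 600 runs per setting.

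| Approximate ICC | Rejections at nominal 5% |
|---|---|
| 0 | 6.3% |
| 0.005 | 4.7% |
| 0.02 | 12.7% |
| 0.04 | 17.3% |
| 0.11 | 32% |

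Monte Carlo error is about 1 to 2 percentage points. The simulation agrees with the formula: no detectable inflation at an ICC near 0.005 or below, and clear inflation from about 0.02 upward.

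**The case against.** The strongest reply is that the article is silent rather than wrong. Negative binomial regression is a family of models that admits random effects, robust standard errors and an exposure term. The authors show elsewhere that they mean to handle clustering, and they refer to a separate trial protocol and a future analysis plan, neither of which is shown. The 2-year linked costs also feed the modelled analysis, so these data are not clearly outside that plan. This stands in part: nothing in the article says that clusters will be ignored. But the article states the adjustment for one analysis and not for another, and its sentence on the analysis plan does not name this comparison. The gap therefore cannot be left to that plan on the wording given.

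It is also fair that this is a secondary question. The word primary in the resource utilisation section ranks outcomes within that section only. The primary economic question, at 6 months, is covered by the clustering sentence.

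Some stronger readings are tempting but not supported:

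- **That the rates themselves are wrong for want of an offset.** A rate already implies a time denominator, and an offset is a detail that an article commonly leaves to an analysis plan. Deaths are foreseen ("In the instance that a participant passes away during the trial, they will be assigned a health utility score of 0 from that point forth"), which makes it useful to define person-time, but no error in the rates is shown.
- **That 2-year data are cut short.** The article says "Study recruitment commenced in February 2024 and is expected to finish by December 2025" and "Participant follow-up is expected to be completed in December 2026". A reader might infer that late recruits have only 12 months of linked data and that a later extract is required. The second date concerns participant follow-up. Utilisation comes from administrative linkage, for which the article sets no end date.
- **That costs are tested without adjustment.** This section describes costs and tests only rates.
- **That adjustment for prior service use is needed.** The article does not mention pre-recruitment records, and their absence is not an error.

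**Conclusion.** The point holds for clustering. The only stated between-group method for 2-year service use in this cluster randomised trial carries no cluster adjustment, and neither the clustering sentence nor the announced analysis plan expressly covers it.

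The size is conditional on two things: that the model is fitted as written, and that the ICC for service use exceeds 0. Under the assumed range of 0.01 to 0.10, a nominal 5% test would have a true size of about 8% to 28%. With an ICC near 0.005 or below the omission would matter little. The calculation takes equal clusters of 24. The point concerns the precision of a secondary comparison; it does not show bias in the rates and does not touch the primary 6-month analysis.

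**What to change.** In *Comparison of resource utilisation*, state that rates will be compared by negative binomial regression with either a team-level random effect or cluster-robust standard errors with a small-sample correction for 30 clusters, and with log person-time as the exposure term. The correction matters because uncorrected robust standard errors tend to be too small with this few clusters. Add that any between-group comparison of costs will use the same clustering structure.

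In *Economic evaluation overview*, extend the scope of the statistical analysis plan to include the 2-year resource utilisation comparison.

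This takes a few sentences and no new data. The price is wider confidence intervals and less power for this comparison.
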